# THE INTERVENTION

## Description of the Alive & Thrive Program in Bangladesh

A&T’s mandate is to facilitate change for improved IYCF practices at scale; to document how interventions are delivered, how much impact can be achieved and at what cost, and to disseminate the evidence and lessons learned so that others can adapt and replicate the cost-effective components.

The goal of the A&T initiative is to reduce avoidable death and disability due to suboptimal IYCF. The specific objectives include an increase in exclusive breastfeeding (EBF) until 6 months of age and reduce stunting by delivering IYCF interventions to caregivers and families of children 0-24 months of age. A&T’s overarching model is based on the assumptions that sustainable improvements in breastfeeding and complementary feeding is achievable through strategies that improve the policy and regulatory environment to support IYCF interventions and practices.

The major goals of the A&T initiative in Bangladesh were to achieve the following in project areas:

1. Increase exclusive breastfeeding (EBF) by 49 percent (from 43 percent to 65 percent) among infants 0-5.9 months of age.
2. Reduce stunting by 10 percent (from 43 percent to 39 percent) among children of age 24-47.9 months.
3. Reduce anemia by 10 percent (from 50 to 45 percent) among children 6-23.9 months of age.

In Bangladesh, A&T’s comprehensive delivery model in Bangladesh largely consisted of a community component implemented through BRAC’s Essential Health Program (EHC) supported by a national advocacy component and a mass media communication strategy [[7](#_ENREF_7)]. A&T also worked in partnership with other local and international NGOs to intensify and scale up activities on infant and young child feeding (IYCF) at the national level as well as to guide the Government of Bangladesh (GOB) in mainstreaming nutrition into the five-year health sector plan. The A&T model also included efforts to actively engage private sector entities to broaden sources of investment for IYCF-related services. Advocacy component of the A&T focused on journalists, the press/media, medical and education sector leaders, and donors funding the next health sector strategy.

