In Bangladesh, 100 sub-districts, across five of six divisions, were selected by BRAC as possible A&T intensive areas based on high poverty and stunting levels, and sub-districts that were not included in the government National Nutrition Program. This list was narrowed to 78 based on geographic proximity, size, and other operational aspects to ensure homogeneity across the sample. Within each division, four sub-districts were then randomly selected for inclusion in the evaluation sample using a computer program, for a total of 20 sub-districts. Sub-districts within each division were then randomly assigned, using a computer program, to either the *intensive* (10 sub-districts) or *non-intensive* (10 sub-districts) intervention. The randomization process was carried out in the presence of BRAC and A&T staff and the program evaluators in BRAC’s headquarters in Dhaka.

The baseline survey was conducted in 20 rural *upazilas* that are part of BRAC’s Essential Health Care (EHC) program platform for A&T. The baseline survey had three components—(i) household survey, (ii) community survey, and (iii) staff survey.

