## Sample size and power calculations

Sample sizes were estimated based on detectable differences between A&T and non-A&T *upazilas* for three separate sets of indicators: 1) exclusive breastfeeding (EBF) rates, 2) complementary feeding practices, and 3) stunting. Our sample size estimates accounted for randomization at the cluster (i.e., *upazila*) level rather than at the individual level. Surveys are repeated cross-sectional, surveying different households/children from the same communities.

The estimated sample sizes for each treatment arm, calculated prior to the baseline survey, was 500 infants 0-5.9 months old for EBF, 500 children 6-23.9 months old for complementary feeding-related practices, and 1,100 children 24-47.9 months old for stunting. Thus, the total proposed sample size was 4,200 children 0-47.9 months old. This sample size was estimated to allow us to detect expected differences in the outcomes outlined below, in a total of 20 clusters with an inter-cluster correlation (ICC) of 0.005, a significance level of 0.05, and power of 80 percent.

A sample size of 500 children aged 0-5.9 months of age was deemed sufficient to detect an increase in EBF rates by approximately 49 percent (from 43 percent to 64 percent); a sample size of 500 children aged 6-23.9 months of age is sufficient to detect an increase in several complementary feeding practices by at least 25 percent; a sample size of 1,100 children aged 24-47.9 months of age is sufficient to detect a reduction in stunting by 15 percent (from 43 percent to 36.5 percent).

Detailed sample size calculations are presented in **Table 3**.

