**Table 3: Sample size calculation for household survey**

|  | **Baseline sample size (same proposed for endline)** | **Baseline (%)** | **Detectable difference with sample size proposed for endline survey**** | **Intra-class correlation at baseline (estimated at upazila level)** | **Minimum sample size for detectable differences** |
| --- | --- | --- | --- | --- | --- |
| Stunting (24-47.9m) |  | 50.9 | 10 pp | 0.02 | 920 (detecting a 9 pp difference will require double this sample size) |
| HAZ (24-47.9m) |  | -2.0±1.2 | 0.35 | 0.05 | 519 |
| EBF (0-5.9m) |  | 49.9 | 20.0 | 0.12 | 390 |
| Minimum acceptable diet (6-23.9m) |  | 14.8 | 10 | 0.04 | 323 |
| Anemia among children  6-23.9 mo |  | 74.7 |  | 0.00 | 284 |

**Based on at least maintaining levels seen in the PE 2013 survey (where data available; data on stunting and anemia not available in PE 2013).*

***Detectable differences are estimated for endline-only comparisons between A&T-intensive and A&T-non intensive; double difference estimates will ensure greater statistical power.*

For the FLW survey at endline, we will again interview BRAC frontline workers delivering services in the 200 villages covered in the sampling for the evaluation. We estimate that the interviews would cover up to 300 SS, 100 SK, and 100 PK.

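### The 80% power stated for stunting, and Table 3's stunting and HAZ sizes, are reached only with an undeclared one-sided 5% test; two-sided, the stated stunting claim has about 71% power

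*Combined protocol and SAP*

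**What the plan says.** The section Sample size and power calculations gives sizes per arm of 500 (0-5.9 months), 500 (6-23.9 months) and 1,100 (24-47.9 months), calculated before the baseline survey, "in a total of 20 clusters with an inter-cluster correlation (ICC) of 0.005", with "a significance level of 0.05, and power of 80 percent". It then states that "a sample size of 1,100 children aged 24-47.9 months of age is sufficient to detect a reduction in stunting by 15 percent", from 43% to 36.5%, and that 500 per arm are enough for EBF to rise from 43% to 64%.

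Table 3 revisits this with baseline levels and ICCs: stunting 50.9%, 10 points, ICC 0.02; HAZ SD 1.2, difference 0.35, ICC 0.05, minimum 519; EBF "49.9 | 20.0 | 0.12 | 390"; minimum acceptable diet 14.8%, 10 points, ICC 0.04, minimum 323. The stunting minimum reads "920 (detecting a 9 pp difference will require double this sample size". A footnote says that the differences are for endline-only comparisons between arms and that the double difference will have more power. No calculation supports that last statement.

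Neither this section nor the Statistical Analysis Plan says whether tests are one- or two-sided.

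**The concern.** An unqualified 5% significance level is normally read as two-sided. On that reading the stunting claim does not follow from its own inputs. HAZ and stunting are the main outcomes named under Evaluation Design, so a non-significant result would be judged against a claimed 80% that the design may not have. The planning ICC of 0.005 is also well below the baseline values of 0.02, 0.05, 0.12 and 0.04 that Table 3 reports for stunting, HAZ, EBF and diet. The section still presents the earlier stunting statement as current and refers to Table 3 for detail.

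**Working it through.** **Inputs.** 20 sub-districts, 10 per arm (Evaluation Design); sizes, rates and ICC 0.005 from Sample size and power calculations; baseline levels, differences and ICCs from Table 3. Two assumptions: the endline sizes are the 1,100 and 500 per arm given in the text, because Table 3's sample-size column is blank as read; and Table 3's minimum sizes are per arm.

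**Formulas.** Design effect DE = 1 + (n/10 − 1)·ICC. SE² = (v1 + v2)/n · DE, with v = p(1 − p) or SD². Power = Φ(d/SE − z), with z = 1.645 one-sided and 1.960 two-sided; the t version is noncentral t with 18 df. With 10 clusters per arm, n = n0(1 − ICC)/(1 − n0·ICC/10), where n0 is the individually randomized size. There is no finite n if n0 reaches 10/ICC.

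**The stunting claim (43% v 36.5%, 1,100 per arm, ICC 0.005).** DE = 1 + 109 × 0.005 = 1.545. v1 + v2 = 0.2451 + 0.2318 = 0.4769. SE = √(0.4769/1,100 × 1.545) = 0.02588. d/SE = 0.065/0.02588 = 2.512.
- One-sided: Φ(2.512 − 1.645) = 81%. This reproduces the plan.
- Two-sided: Φ(2.512 − 1.960) = 71%; with t, 66%.
- Two-sided size for 80%: n0 = 7.849 × 0.4769/0.065² = 886, so n = 886 × 0.995/(1 − 0.443) = about 1,580. Pooled-variance and continuity-corrected variants go up to 1,692.
- At Table 3's ICC of 0.02: DE = 3.18, SE = 0.0371, d/SE = 1.751. Power is 42% two-sided and 54% one-sided.

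**Table 3's minimum sizes.**
- Stunting, 10 points: one-sided with continuity correction, n0 = 325.7 and n = 916, against 920. For 9 points, n = 1,973, about double. Two-sided, 10 points needs 1,657 to 2,184, and 9 points needs about 10,700 or has no finite solution, depending on the formula.
- HAZ: one-sided n0 = 145.4 and n = 505, against 519. Two-sided, n = 2,266.
- EBF: one-sided n = 429 uncorrected, against 390, so no exact match, though one-sided power at 390 is 79.5%.
- Diet, as a 10-point increase: one-sided n = 817 or more, against 323; one-sided power at 323 is 69%. This entry reproduces on neither reading.
- Anemia lists no difference and cannot be checked.

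**Two-sided power for Table 3's differences, endline only.**

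| Outcome | n per arm | DE | d/SE | Normal / t18 |
|---|---|---|---|---|
| Stunting, 10 points | 1,100 | 3.18 | 2.653 | 76% / 71% |
| HAZ, 0.35 | 1,100 | 6.45 | 2.693 | 77% / 72% |
| EBF, 20 points | 500 | 6.88 | 2.513 | 71% / 66% |
| Diet, 10 points | 500 | 2.96 | 2.325 | 64% / 59% |

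**ICC rounding.** At 1,100 per arm, stunting has 83% power if the ICC is 0.015 (DE 2.635, d/SE 2.914) and 69% if it is 0.025 (DE 3.725, d/SE 2.451). HAZ has 80% at 0.045 (DE 5.905, d/SE 2.815) and 73% at 0.055 (DE 6.995, d/SE 2.586). These use the normal approximation.

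**EBF ceiling.** At ICC 0.12 the effective size cannot exceed 10/0.12 = 83.3 per arm. From 49.9% to 69.9%, n0 = 7.849 × 0.4604/0.2² = 90.3. With unlimited children, SE = √(0.4604 × 0.12/10) = 0.0743 and power is Φ(2.691 − 1.960) = 77% (t: 72%). The ceiling depends on the comparison level. Assumed levels of 60%, 65% and 70% need 1,188, 374 and 176 per arm two-sided.

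**EBF 43% to 64%, 500 per arm.** At ICC 0.005, d/SE = 6.10 and power exceeds 99%. At ICC 0.12, d/SE = 0.21/0.0809 = 2.596 and power is 74%.

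**Double difference.** Var = 2[2(1 − ρ)·ICC·v/10 + 2(1 − ICC)·v/n], where v is p(1 − p) at the mean of the two rates and ρ is the upazila autocorrelation between surveys, which the plan does not give. For assumed ρ of 0, 0.5, 0.75 and 0.9, two-sided power is 46%, 64%, 77% and 86% for stunting (10 points), and 41%, 64%, 84% and 96% for EBF (20 points).

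**The case against.** The hypotheses under Objectives are directional, so a one-sided test may have been intended, and on that reading the stunting and HAZ figures are sound. This is fair: the defect is the undeclared sidedness, and the arithmetic is wrong only if the test is two-sided. But directional hypotheses do not declare a one-sided 5% test, and diet's 323 fails either way.

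The figures in the text predate the baseline, and Table 3 updates the ICCs. That explains the 0.005, but the stunting statement is not marked as superseded.

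Table 3 is endline-only, while the planned estimate is a double difference with village fixed effects. This stands as a limit: the figures above do not show what power the planned analysis has. Nor do they support the footnote. On the assumed values, the double difference only matches the endline-only stunting figure at an autocorrelation of about 0.75.

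The 18 df are a conservative reference, since the plan uses child-level models, so both versions are given.

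Four stronger readings are tempting, and the documents do not support them:
- That none of the plan's differences reaches 80% two-sided. EBF 43% to 64% does, easily, at the stated ICC.
- That 20 upazilas rule out 80% for stunting and HAZ. They fall short at the planned sizes, and not if the ICC is really 0.015 or 0.045.
- That a 20-point EBF difference is out of reach at any sample size. This holds from 49.9%. A Table 3 footnote refers to levels in a 2013 survey that are not given, and a comparison level of about 65% or more would allow 80% on the normal approximation.
- That the plan claims power for the programme goal, "Reduce stunting by 10 percent (from 43 percent to 39 percent) among children of age 24-47.9 months". The power section sets 6.5 points and never claims 4.

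**Conclusion.** The point holds in this form. If the test is two-sided, the stated 80% for stunting 43% v 36.5% is about 71% (66% with t), and 42% at the baseline ICC of 0.02. The 920, its doubling for 9 points and the 519 are one-sided figures. Power for the four Table 3 differences is 64% to 77% at the planned sizes. The diet and EBF shortfalls are the firmest: EBF is capped at 77% from 49.9%, and an ICC of 0.115 lifts that cap only to 78%. Those for stunting and HAZ are modest and within ICC rounding. The text's EBF claim stands at ICC 0.005 but falls to about 74% at 0.12.

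The conclusion rests on the unadjusted endline-only comparison that Table 3 uses, on 10 upazilas per arm, and on the sizes being per arm. Power for the planned double-difference analysis is unknown from the documents.

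**What to change.** 1. State the sidedness of the test and whether Table 3's sizes are per arm.
2. If two-sided, replace the stunting power statement and Table 3's differences by those detectable with 80% power at 1,100/500 per arm and the baseline ICCs (normal to t18): stunting about 10.6-11.1 points, HAZ 0.36-0.39, EBF 22-23 points from 49.9%, diet 12-13 points. These solve power = 80%; for HAZ on the normal approximation, 2.802 × 0.12995 = 0.364.
3. If two-sided, mark EBF 20 points as not attainable on the endline-only comparison from 49.9%, or state the comparison level assumed. Correct the 920 and its doubling note.
4. If one-sided, declare it and justify it; 920 and 519 can then stand.
5. On either reading, correct diet's 323 and mark the statements based on ICC 0.005 as pre-baseline.
6. Replace the footnote's assurance about the double difference by a calculation for the planned model under a stated upazila autocorrelation.

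The cost is wording and table figures, one further calculation, and a less favourable stated power. No extra children are needed.

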**Table 3: Sample size calculation for household survey**

|  | **Baseline sample size (same proposed for endline)** | **Baseline (%)** | **Detectable difference with sample size proposed for endline survey**** | **Intra-class correlation at baseline (estimated at upazila level)** | **Minimum sample size for detectable differences** |
| --- | --- | --- | --- | --- | --- |
| Stunting (24-47.9m) |  | 50.9 | 10 pp | 0.02 | 920 (detecting a 9 pp difference will require double this sample size) |
| HAZ (24-47.9m) |  | -2.0±1.2 | 0.35 | 0.05 | 519 |
| EBF (0-5.9m) |  | 49.9 | 20.0 | 0.12 | 390 |
| Minimum acceptable diet (6-23.9m) |  | 14.8 | 10 | 0.04 | 323 |
| Anemia among children  6-23.9 mo |  | 74.7 |  | 0.00 | 284 |

**Based on at least maintaining levels seen in the PE 2013 survey (where data available; data on stunting and anemia not available in PE 2013).*

***Detectable differences are estimated for endline-only comparisons between A&T-intensive and A&T-non intensive; double difference estimates will ensure greater statistical power.*

For the FLW survey at endline, we will again interview BRAC frontline workers delivering services in the 200 villages covered in the sampling for the evaluation. We estimate that the interviews would cover up to 300 SS, 100 SK, and 100 PK.

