# EVALUATION DESIGN

The impact evaluation of community component A&T interventions delivered through the EHC program uses a cluster-randomized design with repeated cross-sectional surveys at the baseline and endline (Figure 3). For the impact evaluation of A&T’s community-based rural platform, 20 rural subdistricts (*upazilas*) that were part of BRAC’s Essential Health Care (EHC) program platform for A&T were purposively chosen. The objective of this impact evaluation model is to capture the synergistic impact of A&T’s community component along with media communications and private-sector activities, such as the promotion and integration of micronutrient powders.

The impact evaluation is designed to capture impact on all key A&T indicators (stunting, infant and young child feeding (IYCF), and anemia). Using a repeated cross-sectional survey design, impact on stunting will be assessed in children 24-48 months old. The impact on other IYCF practices and anemia will be assessed in children 6-23.9 months old; and the impact on exclusive breastfeeding (EBF) will be assessed in children 0-5.9 months old. A double difference impact analysis as well as analysis by exposure level to interventions will be employed to determine the impact of A&T interventions.

The baseline survey was in April to July 2010, and an endline survey is planned for April to July 2014.

The main outcomes being examined are changes in mean height-for-age Z-score (HAZ) and changes in the prevalence of childhood stunting between baseline and the post-intervention survey. Other core impact indicators for A&T in Bangladesh include changes in age-appropriate WHO-recommended IYCF practices among children under 2 years of age (EBF for children 0-5.9 months old and breastfeeding + age-appropriate complementary feeding for children 6-23.9 months old) and anemia among children 6-23.9 months of age.

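### Table 3's minimum of 519 children for HAZ does not fit a two-sided 5% test at 80% power, and the test basis behind it is not declared

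*Combined protocol and SAP*

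**What the plan says.** The Evaluation Design section places HAZ among the main outcomes: "The main outcomes being examined are changes in mean height-for-age Z-score (HAZ", alongside stunting prevalence. The HAZ row of Table 3 reads "2.0±1.2 | 0.35 | 0.05 | 519". The stunting row gives a minimum of "920 (detecting a 9 pp difference will require double this sample size".

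The Sample size and power calculations section states "a significance level of 0.05, and power of 80 percent" for the calculation made before baseline, "in a total of 20 clusters", with 1,100 children aged 24-47.9 months per arm. The Evaluation Design section gives the split as "10 sub-districts) or *non-intensive* (10 sub-districts) intervention". A footnote limits Table 3's detectable differences to endline-only comparisons between the two arms and says that the double-difference estimates will have more power. Neither the sample-size section nor the Statistical Analysis Plan says whether tests are one- or two-sided. Table 3 states no alpha or power of its own. The sample-size text covers EBF, complementary feeding and stunting, so Table 3 is the only sizing statement for HAZ.

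**The concern.** A reader who sets 519 beside 1,100 will conclude that the study has about twice the children that HAZ needs. An unqualified 5% level is conventionally read as two-sided, and on that reading the printed inputs do not lead to 519.

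The stated sensitivity for a main outcome is at stake, and with it how a null HAZ result would be read. The stunting note raises the same issue: it suggests that doubling the sample would buy one more percentage point, and that holds only on the undeclared basis.

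**Working it through.** **Inputs.** From Table 3: SD 1.2, difference 0.35, upazila ICC ρ = 0.05. From the Evaluation Design section: k = 10 upazilas per arm. From the sample-size section: alpha 0.05, power 80% and 1,100 per arm. Assumptions: alpha and power carry over to Table 3, and 519 is per arm, as the sizes in the text are. Table 3's column for the actual sample shows no figures in the copy read, so 1,100 is the pre-baseline plan.

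**Formulas.** Individually randomised size per arm: n0 = 2·SD²·(z_α + z_β)²/d². With a fixed number of clusters: n = n0(1 − ρ)/(1 − n0·ρ/k).

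**Reproducing 519.**

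| Basis | z_α + z_β | n0 | n per arm |
|---|---|---|---|
| One-sided 5%, 80% power | 2.486 | 145.4 | 145.4 × 0.95/(1 − 0.727) = 505 |
| Two-sided 5%, 70% power | 2.484 | 145.1 | 145.1 × 0.95/(1 − 0.726) = 502 |
| Two-sided 5%, 80% power | 2.802 | 184.5 | 184.5 × 0.95/(1 − 0.923) = 2,266 |

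The results are from unrounded values. With SD 1.205, which still rounds to 1.2, the first two rows become 521 and 518, so 519 fits either.

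**Can rounding rescue a two-sided reading?** No. With SD 1.15, ICC 0.045 and difference 0.3549, all at their favourable limits, the two-sided minimum is still about 609. The two-sided figure is unstable, however, because n0·ρ/k = 0.92 is close to 1. ICC 0.045 alone gives 1,039, and unfavourable rounding makes the target unattainable.

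**Two-sided power for 0.35.** SE = SD·√(2·DE/n), with DE = 1 + (n/k − 1)ρ.
- n = 519: DE = 3.545, SE = 0.1403, 0.35/SE = 2.495. Power is 70% (normal) or 66% (noncentral t, 18 df).
- n = 1,100: DE = 6.45, SE = 0.1300, 0.35/SE = 2.693. Power is 77% (normal) or 72% (t). The detectable difference at 80% is 2.802 × 0.1300 = 0.364 (normal) or 0.385 (t).
- n without limit: SE tends to 1.2·√(2 × 0.05/10) = 0.12. Power tends to 83% (normal) or 79% (t). At the printed values, with t on 18 df, no number of children in 20 upazilas reaches 80%.

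**Stunting row** (ICC 0.02; pooled two-proportion formula, then the same cluster formula).

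| Difference | One-sided 5%, 80%, continuity-corrected | Two-sided 5%, 70%, corrected | Two-sided 5%, 80% (uncorrected; corrected) |
|---|---|---|---|
| 50.9% v 40.9% | 916 | 915 | 1,710; 2,184 |
| 50.9% v 41.9% | 1,973 | 1,967 | 12,275; unattainable |

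The printed 920, and its doubling to 1,840 for 9 points, follow the same pattern as HAZ.

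**Rows that do not fit.** At 80% power with a one-sided 5% test, EBF (49.9% to 69.9%, ICC 0.12) needs 429 to 530 uncorrected, or 2,389 and above corrected, against 390 printed. Minimum acceptable diet (14.8% to 24.8%, ICC 0.04) needs 817 to 857, or 1,373 to 1,466, against 323 printed. Two-sided, EBF is unattainable and minimum acceptable diet needs more than 12,000. Neither row reproduces on either basis.

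**The case against.** **The hypotheses are directional, so one-sided tests may be intended.** They are worded that way in the Objectives, but a directional hypothesis does not declare a one-sided test, and the second one names stunting, not HAZ. If one-sided 5% tests are intended, 519 and the 9-point note can stand, but the plan must say so.

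**Alpha and power are stated only for the pre-baseline calculation.** This is correct, and carrying them over is an assumption. The section does introduce Table 3 as its own detailed calculation. If Table 3 used another power, that is also undeclared. If 519 were a total rather than per arm, two-sided power would be about 60%, which is worse.

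**The shortfall at 1,100 is small.** It is: 0.364 or 0.385 against 0.35. Over input rounding, normal two-sided power at 1,100 runs from about 69% to 85%. What fails is the printed minimum and the margin it implies.

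**The planned analysis is a double difference.** So 72-77% is not its power. That power depends on the correlation of upazila means between surveys, which the documents do not give. As an illustration, take variance 2[2·SD²·ρ(1 − r)/10 + 2·SD²(1 − ρ)/1,100]. For assumed r of 0, 0.5, 0.6 and 0.8, normal two-sided power is about 48%, 71%, 78% and 92%. The footnote's gain is possible but not assured.

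**Stronger readings a reader might infer.** One is that 519 can come only from a one-sided test; a two-sided test at 70% power fits equally well. A second is that one hidden basis explains the whole table; two rows contradict this. A third is that 1,100 is half of what HAZ needs; this takes 2,266 as firm, when an ICC of 0.045 brings the figure below 1,100 on the normal approximation. The documents support none of the three.

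**Conclusion.** The printed minimum for HAZ is inconsistent with a two-sided 5% test at 80% power, even with every input rounded favourably (about 609 against 519). It has a four-fold gap at the printed values by normal approximation (2,266), but that multiple is fragile and should not be the headline. The firmer statement is power and detectable difference at 1,100 per arm: 72-77% for 0.35, and 0.36 to 0.39 at 80% power. There is no twofold margin.

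The 920 and the 9-point remark for stunting share the inconsistency. EBF and minimum acceptable diet are unexplained on either basis. All of this rests on the assumed carry-over of alpha and power, on 519 being per arm, on 1,100 being the pre-baseline plan, and on the endline-only comparison that Table 3 describes. It says nothing definite about the power of the double-difference analysis.

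**What to change.** Under Table 3, state sidedness, alpha, power, the test (normal, or t with 18 df) and whether the sizes are per arm. Recompute every row on that one basis.
- If two-sided 5% is used: replace 519 by a statement that 1,100 per arm gives 72-77% power for 0.35, with a detectable difference of 0.36-0.39. Note that adding children within 20 upazilas may not reach 80%. Remove or correct the remark that doubling the sample buys 9 points for stunting.
- If one-sided 5% is intended: declare it in the Statistical Analysis Plan and use it for every hypothesis test.

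The cost is one recalculated table and one sentence. On the two-sided basis the stated sensitivity becomes less favourable. No extra children are needed, and the two-sided restatement leaves the design and the analysis unchanged.

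### Table 3's minimum of 323 children for a 10-point difference in minimum acceptable diet does not follow from the inputs printed in its own row

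*Combined protocol and SAP*

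**What the plan says.** The minimum acceptable diet row of Table 3 reads "Minimum acceptable diet (6-23.9m) | | 14.8 | 10 | 0.04 | 323": baseline 14.8%, detectable difference 10, ICC 0.04, minimum sample size 323. The column header places the ICC at upazila level, which is the level of randomization. The table's footnote fixes the comparison: "Detectable differences are estimated for endline-only comparisons between A&T-intensive and A&T-non intensive". It adds that the double difference will have greater power.

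The section on sample size and power calculations gives "a significance level of 0.05, and power of 80 percent" and does not say whether the test is one- or two-sided. Before baseline it assumed 20 clusters and an ICC of 0.005, and planned "500 children 6-23.9 months old for complementary feeding-related practices" in each treatment arm. The section on evaluation design assigns 10 sub-districts to each arm. Table 3's column for the baseline sample size is blank in the text available.

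**The concern.** With only 10 clusters per arm, an ICC of 0.04 makes the requirement climb steeply, because extra children in the same upazila add little information. A minimum of 323 looks too small for a 10-point difference on that ICC.

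This is Table 3's only row for a complementary feeding outcome, and minimum acceptable diet is one of the impact indicators in Table 6. As printed, a reader would conclude that 323 children give 80% power, and that a plan of 500 per arm has ample margin. If the row is wrong, the plan misstates what the endline comparison can detect, and a non-significant result could be read with more confidence than the design supports.

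**Working it through.** **Inputs.** From Table 3: p1 = 0.148, difference 0.10 (so p2 = 0.248), ICC = 0.04, endline-only. From the sample size section: alpha 0.05, power 80%, sizes per arm. From the evaluation design: k = 10 upazilas per arm. Sidedness is unstated, so both are tried. Table 3 does not say whether 323 is per arm; it is taken as per arm, in line with the sample size section.

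**Step 1, no clustering.** n0 = (z_alpha + z_beta)² × (p1q1 + p2q2) / d², with p1q1 + p2q2 = 0.1261 + 0.1865 = 0.3126.
- One-sided: (1.645 + 0.842)² × 0.3126 / 0.01 = 193.3 (195.3 with pooled variance).
- Two-sided: (1.960 + 0.842)² × 0.3126 / 0.01 = 245.3 (248.1 pooled).

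**Step 2, attempt to reproduce 323.** The design effect is 1 + (m − 1) × ICC with m = N/10. Solving for N gives N = 10 × n0 × (1 − ICC) / (10 − n0 × ICC).
- One-sided: 10 × 193.3 × 0.96 / (10 − 7.73) = 817; pooled, 857.
- Two-sided: 10 × 245.3 × 0.96 / (10 − 9.81) = about 12,660; pooled, about 31,200.
- A continuity correction raises the one-sided need to 1,373 (unpooled) or 1,466 (pooled). Two-sided with pooled variance it leaves no solution, because n0 × ICC = 267.7 × 0.04 = 10.7 exceeds 10.

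None of these is near 323.

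**Step 3, rounding of the printed inputs.** Need per arm for a 10-point difference:

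| ICC | One-sided, unpooled | One-sided, pooled | Two-sided, unpooled |
|---|---|---|---|
| 0.035 | 576 | 596 | 1,676 |
| 0.040 | 817 | 857 | about 12,660 |
| 0.045 | 1,416 | 1,540 | no solution |

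Taking the most favourable corner, ICC 0.035 and a difference of 10.5 points, n0 falls to 176.7 and the one-sided need to 447. That is still above 323, though below 500.

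**Step 4, what would give 323.** With the other inputs as printed, ICC = (323/n0 − 1) / (32.3 − 1). One-sided this is (323/193.3 − 1) / 31.3 = 0.021. Two-sided it is (323/245.3 − 1) / 31.3 = 0.010. These are about a half and a quarter of the printed 0.04.

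**Step 5, endline-only power for 10 points at ICC 0.04.**
- At 323 per arm: design effect 1 + 31.3 × 0.04 = 2.25; effective size 143; SE = √(0.3126/143.4) = 0.0467; 0.10/SE = 2.14. Power is Φ(2.14 − 1.645) = 69% one-sided and Φ(2.14 − 1.960) = 57% two-sided.
- At 500 per arm: design effect 1 + 49 × 0.04 = 2.96; effective size 169; SE = 0.0430; 0.10/SE = 2.32. Power is 75% one-sided and 64% two-sided. The difference detectable with 80% power is about 10.8 points one-sided and 12.3 two-sided.

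**The case against.** The strongest reply is that this row does not describe the planned test. The SAP estimates impact by a double difference with village fixed effects, and the footnote limits Table 3 to endline-only comparisons. This is right as far as it goes. The power of the planned analysis depends on the correlation between rounds, which the plan does not report, and it could be higher or lower than the figures above. A reader might infer that the trial is underpowered for complementary feeding; the documents do not support that. But the footnote also means that double-difference power cannot be the source of 323.

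A second reply is that not every input is visible. A footnote refers to maintaining levels from a 2013 survey, and its marker is not tied to a column in this text, so the difference actually used may not be exactly 10. That stands. At ICC 0.04 an unrounded difference of about 11.8 points would also give roughly 323 one-sided. So a reader might infer that an ICC of 0.02 must have been used, but that follows only if everything else is as printed. A comparison-arm level above 14.8% would raise the need, so it does not rescue the row.

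Third, the 500 per arm was set before baseline with an ICC of 0.005, and the size column is blank. A reader might infer that the achieved sample falls short of the requirement. That needs the actual size, and even at 500 the shortfall disappears in the most favourable rounding corner (447).

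Finally, a reader might infer that the other rows reproduce on one common one-sided formula, leaving this row as the sole exception. They do not. Stunting comes to 916 against 920 only with pooled variance and continuity correction, which gives EBF about 13,930 against 390. EBF comes to 429 only unpooled and uncorrected, which gives stunting 760. The finding on this row does not need that contrast.

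**Conclusion.** The figure of 323 is wrong as written: no standard two-proportion calculation on the row's printed inputs, with 10 upazilas per arm, returns it. At the printed values the need is about 820 to 860 per arm one-sided without continuity correction (576 to 1,540 over ICC rounding; 447 with the difference also at 10.5 points), and over 12,000 two-sided. The width of that range shows how sensitive the answer is to the second decimal of the ICC, so no single replacement number should be treated as exact.

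The conclusion assumes that sizes are per arm; if 323 is a total for both arms, the gap is larger. The power and detectable differences quoted for 500 per arm also assume that the pre-baseline plan was achieved. All of the figures apply to the endline-only comparison. Because the endline size repeats the baseline size, 323 does not itself set enrolment. The harm lies in how the plan's sensitivity is stated and later read.

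**What to change.** Recompute the row from the baseline data and state the formula, the sidedness and whether sizes are per arm.
- If the ICC is 0.04 and the difference 10 points, withdraw 323 and give the detectable difference and power at the actual endline size. For orientation, 500 per arm would detect about 10.8 points one-sided or 12.3 two-sided in an endline-only comparison.
- If another ICC or another difference was used, print it and reconcile it with the baseline estimate.
- Label the result as endline-only, and do not present it as the power of the double-difference analysis.

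The cost is one table row and a short note. On an ICC of 0.04 the stated sensitivity becomes somewhat less favourable. No extra children and no change of design are needed.
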